# 1 Introduction

## 1.1 Scientific and Therapeutic Background

The SARS-CoV-2 disease, also known as coronavirus disease 2019 (COVID-19) is a respiratory illness caused by the newly discovered Severe Acute Respiratory Syndrome Coronavirus 2 (SARS-CoV-2). First cases of COVID-19 were reported in December 2019 . The viral infection subsequently rapidly spread worldwide resulting in a pandemic with severe implications on health care systems due to high morbidity and mortality. The infection is characterized by a mild to moderate respiratory illness in most affected patients. However, older people, and patients with concomitant diseases such as chronic respiratory diseases, cardiovascular diseases, cancers, and/or chronic immunosuppression are at high risk to develop severe respiratory distress .

Current control strategies of SARS-CoV-2 disease are limited to prevention, case monitoring and supportive care. A validated vaccine or curative treatment is not available yet, resulting in disease widespread and increasing mortality . Therefore, novel therapeutic options are urgently needed. Outbreaks have overwhelmed the health care systems in several regions of the world, notably in China (Hebei province), Italy (Lombardy) and in France (Alsace). Patients requiring mechanical ventilation were not intubated due to shortages in ventilators, material and staff . Accordingly, early effective treatment is urgently required to avoid the need for mechanical ventilation.

Over the last past decades, convalescent plasma (CP) has been used for the prevention or treatment of various life-threatening infections, especially respiratory viral infections such as H1N1, H5N1 and the coronaviruses SARS1 and MERS . Recently, encouraging results of the treatment of 5 critically ill COVID-19 patients with convalescent plasma have been reported . There are additional non-peer reviewed reports about benefit in SARS-CoV-2 infected patients . SARS-Cov-2 infection is associated with cytokine changes that may partially drive the pathogenesis of Acute Respiratory Distress Syndrome, ARDS . Plasma therapy has a long standing history with an excellent safety profile . From a theoretical perspective, there are *in vitro* concerns whether antibodies against SARS-CoV-2 might lead to Antibody Dependent Enhancement (ADE) of virus entry into cells .

Thus, there is now accumulating evidence suggesting that passive immunotherapy using CP decreases the morbidity and mortality in SARS and epidemic Influenza . However, these data were gained through retrospective studies, case reports, and CP treatment was usually combined with other drugs . Hence, reliable evidence of the association of CP treatment with favourable clinical course – particularly in SARS-Cov-2 infections – has not been properly demonstrated yet.

### 1.1.2 Passive antibody therapy

The principle of passive antibody therapy using infusions of CP is based on the fact that following infection with an infectious agent, the infected person produces specific antibodies against the latter. Thus, CP obtained from subjects, who have recovered from an infection provides a specific prophylactic or therapeutic weapon against the corresponding infectious agent. Unlike vaccination, passive antibody therapy provides an immediate protection . This is of particular importance in an infectious outbreak context, especially for high-risk, patients who might not develop a prompt and adequate immune response due to underlying diseases or concomitant therapies.

## **1.2 Trial Rationale/ Benefit- Risk Assessment**

### **1.2.1 Trial Rationale**

The aim of this randomized phase-II study is to gain evidence on the effect of CP in the treatment of SARS-CoV-2 infection in high-risk patients. High-risk is defined within 4 groups; group 1, pre-existing or concurrent hematological malignancy and/or active cancer therapy (incl. chemotherapy, radiotherapy, surgery) within the last 24 months or less; group 2, chronic immunosuppression not meeting the criteria of group 1; group 3, age  $\geq 50$ -75 years and meeting neither the criteria of group 1 nor group 2 and lymphopenia  $< 0.8 \times G/l$  and/or D-dimer  $> 1\mu g/mL$ ; group 4, age  $\geq 75$  years and meeting neither the criteria of group 1 nor group 2). The main focus of the protocol is to assess the clinical outcome in high-risk patients after infusion of CP in patients with confirmed SARS-CoV-2 infection and a  $O_2$  saturation  $\leq 94\%$  while breathing ambient air. Patients requiring mechanical ventilation and/or extracorporeal membrane oxygenation (ECMO) are not eligible for the trial.

Based on previous studies, we hypothesize that an infusion of CP relatively early during the SARS-CoV-2 infection might reduce the severity of the disease rapidly and thus avoid a progression to a more severe disease state and death.

### **1.2.2 Benefit - Risk Assessment**

Currently, clinical management of high-risk COVID-19 patients remains a challenge . In general, treatment of SARS-CoV-2 infections is purely symptomatic and depends on the underlying diseases. After failure of supportive care, there are currently no approved options available for these patients; clinical studies with remdesivir, hydroxychloroquine and tocilizumab are ongoing while a randomized study lopinavir-ritonavir was negative .

Taking into consideration the beneficial safety profile, infusion of CP may offer access to a potentially effective therapy in high-risk patients whose treatment options are limited .

## **1.3 Reference Committees**

### **1.3.1 Data Monitoring Committee (DMC)**

The DMC is composed of at least three independent experts, assessing the progress and safety data. The mission of the DMC is to ensure the ethical conduct of the trial and to protect the safety interests of patients in this trial.

The DMC meetings are planned after treatment of 5, 10 and 25 patients in the experimental arm of the study and according to the DMC charter. Based on its review, the DMC provides the sponsor with recommendations.

Further details including DSUR reviews and DMC members is specified in the DMC charter.

## **2 Trial Objectives**

### **2.1 Primary Objective**

- To assess the time from randomization until an improvement within 84 days defined as two points on a seven point ordinal scale or live discharge from the hospital in high-risk patients (group 1 to group 4) with SARS-CoV-2 infection requiring hospital admission by infusion of plasma from subjects after convalescence of SARS-CoV-2 infection or standard of care

### **2.2 Secondary Objectives**

- To assess overall survival, and the overall survival rate at 28, 56 and 84 days.
- To assess SARS-CoV-2 viral clearance and load as well as antibody titres.
- To assess percentage of patients that required mechanical ventilation.

- To assess time from randomization until discharge

For detailed endpoints see sections 10.3.2. and 10.3.3

### 3 Trial Design

This is a multicentre, randomized, open-label, phase II clinical trial designed to evaluate the clinical outcome in high-risk patients with SARS-CoV-2 infection by infusion of plasma from subjects after convalescence of SARS-CoV-2 infection.

High-risk is defined as SARS-CoV-2 positive infection with Oxygen saturation at  $\leq 94\%$  at ambient air with additional risk features as categorized in 4 groups:

- group 1, pre-existing or concurrent hematological malignancy and/or active cancer therapy (incl. chemotherapy, radiotherapy, surgery) within the last 24 months or less.
- group 2, chronic immunosuppression not meeting the criteria of group 1
- group 3, age  $\geq 50 - 75$  years meeting neither the criteria of group 1 nor group 2 and at least one of these criteria:  
Lymphopenia  $< 0.8 \times 10^9/L$   
and/or  
D-dimer  $> 1 \mu g/mL$
- group 4, age  $\geq 75$  years meeting neither the criteria of group 1 nor group 2

The primary end point is the time to clinical improvement within 84 days, defined as the time from randomization to either an improvement of two points on a seven-category symptom ordinal scale or live discharge from the hospital, whichever comes first. A total of 174 patients are planned to be included into the trial.

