### **6.6 Enrolment, Randomisation, Treatment Assignment**

A subject is considered enrolled when he or she has signed the Informed Consent form. The patient receives a screening number at the clinical site (number of site plus number of patient in ascending order, e. g. 001-001 for the first enrolled patient at site 01) via registration in the eCRF system (www.xxx.). The screening number is used to identify the

---

 This section of the study protocol is defined as reference safety information (RSI).

subject throughout the clinical study and must be used on all study documentation related to the subject.

Clinical sites must complete the baseline case report forms for all enrolled subjects, even if the subject is not randomised or treated in this study.

Upon confirmation of eligibility (patients must meet all inclusion criteria and must not meet exclusion criteria), the clinical site must contact a centralized internet randomization system (<https://randomizer.at/>). Patients are randomized using block randomisation to one of the two arms, experimental arm or standard arm, in a 1:1 ratio considering a stratification according to the 4 risk groups (as described in the inclusion criteria).

All subjects randomised receive a unique randomisation number. All patients in the experimental group have to start CP treatment within 7 days of randomization. Patients withdrawn from the trial retain their Patient ID and randomization number.

The study is open-label.

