### **7.3.1 Seven point ordinal scale**

The seven point ordinal scale value is determined at the time of study inclusion and afterwards until discharge within 84 days after randomization or end of trial. This endpoint was also recommended by the WHO R&D Blueprint expert group (Coronavirus disease (COVID-2019) R&D. Geneva: World Health Organization (<https://www.who.int/blueprint/priority-diseases/key-action/novel-coronavirus/en/>)). The seven-category ordinal scale consists of the following categories: 1, not hospitalized with resumption of normal activities; 2, not hospitalized, but unable to resume normal activities; 3, hospitalized, not requiring supplemental oxygen; 4, hospitalized, requiring supplemental oxygen; 5, hospitalized, requiring nasal high-flow oxygen therapy, noninvasive mechanical ventilation, or both; 6, hospitalized, requiring ECMO, invasive mechanical ventilation, or both; and 7, death.

This scale is clearly defined and values will be obtained daily for each patient until day 28, thereafter weekly until day 56, then on day 70 and finally at day 84. A change in two points is clinically meaningful in either direction. For example, a patient with an improvement from #4 (oxygen supplementation, hospitalized) to #2 (discharged, no oxygen) is clearly relevant. Also, a change from #5 (high flow oxygen) to #3 (hospitalized but no supplemental oxygen) is clearly relevant as well. Of note, inclusion criteria of the trial determine that all patients to be included are either in #4 or #5 at time of inclusion into the trial.

Physicians or nurses record the scale value daily at the same time. The time can be fixed individually for each patient. Recordings are obtained +/- one hour of the intended time.

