## **10.2 Analysis Variables**

### **10.2.1 Primary endpoint and primary estimand**

The main purpose of the study is to assess the time from randomization until an improvement within 84 days defined as two points on a seven point ordinal scale or live

discharge from the hospital in high-risk patients (group 1 to group 4) with SARS-CoV-2 infection requiring hospital admission by infusion of plasma from subjects after convalescence of a SARS-CoV-2 infection or standard of care. .

In the Addendum to the ICH E9 guideline (final version), the estimands framework is recommended as clear and transparent definition of “what is to be estimated” (International Council for Harmonization 2019). An estimand is defined through the treatment, the targeted population, the variable, a specification of how to handle intercurrent events (postrandomization events) and a population-level summary. In the following, the primary estimand corresponding to the primary objective is described.

The primary estimand corresponding the primary objective is defined as follows:

**Treatment:** Infusion of frozen CP (on two days of intervention from two different donors) vs. standard of care (as described in 5.7).

**Population:** The targeted population is defined through the in- and exclusion criteria.

**Variable:** Time from randomisation to clinical improvement within 84 days by two points on a seven point ordinal scale or live discharge from the hospital.

**Post-randomisation events:** live discharge from the hospital is incorporated into the variable definition (composite strategy), death from any cause within 84 days after randomization without previous improvement is taken into account by censoring deceased patients at day 84 (see sections 10.3 and 10.5.4 for rationale) ); treatment switch will be ignored (treatment policy strategy, see sections 10.3 and 10.5.4 for rationale); event-free patients at the end of the follow-up period are censored and drop-outs are censored at the last observation (hypothetical strategy).

**Summary measure:** Hypothesis testing is conducted using a log-rank test. The summary measure for effect quantification is the hazard ratio for the endpoint “clinical improvement by two points or live discharge” between the two treatment arms (which is estimated using Cox regression).

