Since patients might die before experiencing a clinical improvement or being discharged from the hospital, death will be taken into account via censoring deceased patients at last day of follow-up (day 84). Based on recently published data, the mortality rate is assumed to be about 20% in the control arm. Thus, we expect that the cumulative improvement rate of the control group will not become larger than 0.8. Hence, fewer improvement events are expected during the follow-up of 84 days than under the assumption of an exponential distribution, since the improvement curves will flatten at some point. In case of the control group, the flattening is expected to occur at day 38, since the assumed cumulative improvement rate at day 38 amounts to  $\exp(-\lambda_C \cdot 38) = \exp(-0.043 \cdot 38) \approx 0.8$ . Accordingly, we conservatively assume a follow-up length of 38 days for the sample size calculation to properly estimate the probability of experiencing the event of interest, even though the actual follow-up for each patient will be longer.

To detect the assumed difference between treatment groups using a log-rank test comparing the cumulative improvement curves for the primary endpoint using a significance level of 5% (two-sided) with a power of 80%, a total number of 174 patients is required for the entire trial (87 patients per group) when additionally considering a dropout rate of 5%, meaning that n=164 patients who do not prematurely drop out of the study are required to be enrolled. The required number of events which was calculated using the formula by Schoenfeld, amounts to 142. It is expected that adjusting for the covariate “patient group” in the analysis will lead to an increase in power. Sample size calculation was done conservatively assuming an equally long follow-up period of 38 days for every patient. Sample size calculation was done using RPACT v 2.0.6.

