#### **10.5.5 Analysis of the Secondary Endpoints**

Overall survival is analyzed by using a Cox regression model adjusting for treatment and patient group, determining hazard ratios with 95% confidence intervals and (descriptive) p-values. Survival estimates are calculated using the Kaplan-Meier method together with 95% log-log-type confidence bands, and the 28-day survival rate will be given for both treatment groups together with 95% confidence intervals. Analogously as for the supplementary analysis of the primary endpoint, an IPCW model and a RPSFT model will additionally be fitted for the secondary endpoint overall survival to assess the potential treatment effect in case patients had not switched from the control to the experimental arm.

Time until discharge will be assessed similarly to the primary endpoint, providing Kaplan-Meier estimates for the cumulative discharge rate for both treatment groups and conducting a log-rank test stratified for the factor “patient group”, and censoring patients who died from any cause at day 84 in analogy to the analysis of the primary endpoint. Analogously as for the sensitivity analysis of the primary endpoint, an IPCW and a RPSFT model will additionally be fitted for the secondary endpoint ‘time until discharge’ to assess the potential treatment effect in case patients had not switched from the control to the experimental arm.

The secondary endpoint “requirement of mechanical ventilation (yes/no)” is analyzed by means of a logistic regression model adjusting for the factors treatment and patient group. Also, absolute and relative frequencies will be given for this endpoint, together with 95% confidence intervals.

The secondary endpoints SARS-CoV-2 viral load and antibody titres will be assessed over time by means of linear mixed models adjusting for treatment group, patient group, and

baseline value as fixed factors, as well as time as repeated factor using an unstructured covariance matrix, calculating least square means estimates and 95% confidence intervals.

While it is indirectly assumed by these models that data will be missing at random, i.e. that the missingness can be explained by observed covariate and outcome values, we will assess the robustness of this assumption by means of sensitivity analyses by means of pattern mixture models assuming that data will be not missing at random.

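### The primary endpoint scores every live discharge as clinical improvement, so a patient discharged for end-of-life care counts as improved even if death follows within 84 days

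*Protocol*

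**What the plan says.** Section 3 sets the event as "either an improvement of two points on a seven-category symptom ordinal scale or live discharge from the hospital, whichever comes first". The Summary, the synopsis objectives, and sections 2.1, 4 and 10.2.1 repeat the discharge component without a condition on destination, goal of care or oxygen need. The estimand fixes it too: "live discharge from the hospital is incorporated into the variable definition (composite strategy").

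Section 7.3.1 states that "all patients to be included are either in #4 or #5 at time of inclusion". Category 2 is defined as "2, not hospitalized, but unable to resume normal activities", and categories 3 to 6 all begin with being hospitalized. The same section calls a change "from #4 (oxygen supplementation, hospitalized) to #2 (discharged, no oxygen) is clearly relevant". The category definitions themselves (section 7.3.1, footnote 9 of the trial schedule, Appendix 18.1) carry no oxygen condition for category 1 or 2.

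Death is handled separately. Section 10.2.1 censors at day 84 those who die within 84 days without having improved first. Section 10.5.4 gives the purpose: deceased patients are to be treated as not improved over all 84 days.

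For the secondary endpoint, "Time until discharge will be assessed similarly to the primary endpoint". Section 6.6 adds: "The study is open-label". The protocol mentions neither hospice or palliative discharge nor transfer to another hospital.

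**The concern.** The endpoint is meant to measure recovery, and the day-84 rule is there to keep deaths from looking like recoveries. Discharge for end-of-life care gets past that rule: the patient becomes an improvement event on leaving, and the later death no longer changes the primary outcome.

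The population makes this plausible. Eligible patients have malignancy, immunosuppression or age-related risk (section 5.3), and section 10.3 assumes about 20% control mortality. For a patient at category 4, a two-point gain already means leaving hospital, so discharge is the only route to the event. Treating staff know the arm when they decide on discharge, so the rate of miscounting could differ between arms.

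**Working it through.** **1. The rule applied to one record.** Take a patient at category 4 at baseline, sent home for end-of-life care on day 12, who dies on day 18.

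- Discharge limb: left the hospital alive, so an event on day 12.
- Scale limb: not hospitalized and unable to resume normal activities, so category 2. The gain is 4 − 2 = 2, an event on day 12.
- Death rule (10.2.1): applies only without previous improvement, so it does not apply.

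From category 5 the gain is 5 − 2 = 3, with the same result. Putting a condition on the discharge limb alone would change nothing, because the scale limb still fires.

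**2. The protocol's own figures.** These reproduce and are not in dispute. The design is "using a significance level of 5% (two-sided) with a power of 80" percent, hazard ratio 1.6, 1:1 allocation.

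- Events (Schoenfeld): 4 × (1.96 + 0.8416)² / (ln 1.6)² = 142.1; the protocol states 142.
- Event probability by day 38: control 1 − exp(−38 × ln 2 / 16) = 0.807; plasma 1 − exp(−38 × ln 2 / 10) = 0.928; mean 0.868.
- Patients: 142.1 / 0.868 ≈ 164. With 5% dropout, 82 / 0.95 = 86.3, so 87 per arm and 174 in total.

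**3. How many patients could be affected.** The documents give no share, so the shares below are assumptions.

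- Expected deaths: 82 × 0.20 = 16.4 in control. With the 13% used in the section 10.3 simulation, 82 × 0.13 = 10.7 on plasma. Total 27.1.
- If 20-30% of them leave hospital alive first: 5.4 to 8.1 false events in the trial.

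**4. Effect on the comparison.** Each scenario used 4,000 simulated trials with 82 patients per arm and a log-rank test. Improvement times were exponential with medians 16 and 10 days, capped at 0.80 and 0.87. Under no effect, both arms had the control curve. A share of deaths was recoded as events between days 5 and 25.

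| Scenario | Share of deaths miscounted | Hazard ratio | Upper-tail rejection |
|---|---|---|---|
| Protocol effect | none | 1.46-1.47 | not used here |
| Protocol effect | 20-30% in both arms | 1.45-1.47 | not used here |
| No effect | 30% in both arms | not used here | 2.9% |
| No effect | 5% control, 10% plasma | 1.03 | 4.0% |
| No effect | 20% control, 30% plasma | 1.06 | 5.4% |
| No effect | 10% plasma only | 1.05 | 4.7% |
| No effect | 20% plasma only | 1.11 | 8.6% |
| No effect | 30% plasma only | 1.16-1.17 | 13.1-14.8% |

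The nominal upper tail is 2.5%. Ranges come from separate runs. The run behind the two unequal-share rows gave 3.0% with no miscount. With 20% and 30% miscounted in both arms under the protocol effect, events rise from 137 to 142 and 145.

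**5. Transfers and oxygen, from the text alone.** A patient moved to another acute hospital has left the recruiting hospital but is still hospitalized, hence in category 3 to 6. The discharge wording and the scale can point in different directions, and the protocol does not choose. For discharge on oxygen, the section 7.3.1 example describes category 2 as without oxygen, while the definition does not mention oxygen.

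**The case against.** **Frequency and symmetry.** The documents give no rate of palliative discharge. If it is the same in both arms, the comparison barely moves. The larger figures need the miscount to fall on one arm only, and the text supplies no mechanism for that beyond open-label treatment. This stands: those figures are a bound, not an estimate.

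**The death rule may already cover it.** Section 10.5.4, read alone, censors deceased patients at day 84 and could be taken to override an earlier discharge. Section 10.2.1 does not allow this, since it limits the rule to deaths without previous improvement, and section 10.3 speaks of patients who died without an improvement. Read literally, the override would also erase a real recovery followed by a later death.

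**Visibility.** Overall survival and the 28-, 56- and 84-day survival rates still record these deaths. That helps interpretation but does not correct the primary test.

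**Operational detail may sit elsewhere.** The SAP and the CRF completion guidelines are not shown. The endpoint and estimand are nevertheless fixed in the protocol, without a condition.

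**Stronger readings that the documents do not support.**
- A reader might infer that transfers to another hospital are scored as improvement. Nothing says so; a transferred inpatient is still in a hospitalized category. It is an ambiguity that centres could resolve differently, not a stated rule.
- A reader might infer that discharge on oxygen is plainly an event. The only text on oxygen at discharge, the section 7.3.1 example, points the other way. The finding is a mismatch between example and definition.
- A reader who rebuilds the capped model will see rejection near 60% under the protocol's effect. That belongs to the illustration. The protocol states 80% and simulates 0.785 in the matching row of Table 3, so no power deficit is argued here.

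**Conclusion.** The point holds for discharge for end-of-life care. The discharge limb and the scale limb both score it as improvement, the death rule does not undo it, and the result contradicts the purpose given in section 10.5.4. For transfer the protocol is ambiguous; for discharge on oxygen it is inconsistent.

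The size is unknown from the documents. Equal shares leave the hazard ratio almost unchanged. With moderately unequal assumed shares under no effect, it is 1.03 to 1.06 with an upper tail of 4.0% to 5.4%. The assumed one-arm bound, with 10-30% of deaths miscounted, gives about 1.05-1.17 and about 5-15% against 2.5%. These figures rest on the protocol's medians and control mortality and on the assumed shares and timing.

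The main harm is to what the endpoint means, with possible differential bias because discharge is decided unblinded. It should be corrected, and the correction is cheap. The sample size is not affected.

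**What to change.** In sections 3, 7.3.1, 10.2.1 and 10.5.4, and wherever the Summary, synopsis and sections 2.1 and 4 repeat the endpoint:

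- State that discharge for palliative or end-of-life care is not an event under either limb, live discharge or two-point gain, and is censored at day 84 like death without improvement. Requiring category 1 or 2 on leaving is not enough, because a patient sent home to die is in category 2.
- State that transfer to another acute hospital is not discharge and that scale scoring continues there. The trial schedule now stops the scale at hospital discharge, so it should say the same.
- Reconcile the section 7.3.1 example with the category definitions in section 7.3.1, footnote 9 and Appendix 18.1, so that discharge on oxygen has one classification.
- Apply the same rules to time until discharge in section 10.5.5.

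The cost is endpoint wording and one eCRF item for discharge destination. Transferred patients need scale values from the receiving hospital; the contacts with patients or treating physicians planned in section 8 can be extended to obtain them. There will be slightly fewer or later events.
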